## Abstract

Tobacco addiction is the primary preventable factor contributing to global mortality, and nicotine is one of the substances with the greatest potential for addiction. With a strong affinity for the α4β2 subtype receptor, cytisine (CYT) functions as a partial agonist of the acetylcholine nicotinic cholinergic receptor. It counteracts the effects of nicotine without causing any withdrawal symptoms. These features, combined with its limited mild adverse effects and minimal drug–drug interactions, make cytisine a cost-effective treatment for smoking cessation. The current protocol describes a prospective observational study on the safety and efficacy of CYT administered to inpatient smokers of the Integrated University Hospital of Verona (IUHVR), Veneto (Italy). This is a monocentric, observational, and prospective study on both sex smokers over the age of 18 years admitted to the IUHVR who meet the criteria for recruitment and have given their consent. Eligible participants will be assigned to the CYT intervention based on the West dosing schedule and will be followed up for 12 months from treatment initiation. Evaluation of safety, efficacy, and compliance will be assessed at 7 and 25 days, with follow-up at 3, 6, and 12 months from the start of the treatment (quit day). During each visit, any adverse events or adverse reactions reported by patients following the intake of CYT will be evaluated. This study will contribute, for the first time, to the knowledge about the use of CYT for smoking cessation in a hospital setting.

## Introduction

Cigarette smoking stands as the primary avoidable factor responsible for diseases and premature mortality on a global scale. According to the World Health Organization (WHO), smoking causes the deaths of over eight million people annually (1, 2). A total of 1.18 billion individuals smoked cigarettes in 2020, with a global smoking prevalence of 6.5% among women and 32.6% among men, causing 7 million deaths (2).

Smoking is responsible not only for several neoplastic pathologies, such as lung cancer, but also for non-neoplastic diseases, among others chronic obstructive pulmonary disease (COPD) and cardiovascular diseases (3). In Italy, approximately 50% of smokers die prematurely because of smoking-related diseases, and data relating to the younger population are particularly alarming (4).

Nicotine, an alkaloid (1-methyl-2-43 [3-pyrodyl] pyrrolidine), is the predominant pharmacological substance implicated in tobacco addiction, and its effect is related to binding the cholinergic receptors, which are involved in the addiction mechanism due to dopamine release. Like all other pathologies, nicotine addiction is a clinical condition that requires medical care and must be treated using pharmacological and non-pharmacological strategies (1).

Pharmacological treatments for tobacco addiction act on the dopaminergic and cholinergic systems in order to prevent or reduce nicotine withdrawal symptoms (5). Nicotine substitutes (nicotine replacement therapy, NRT), bupropion, varenicline, and cytisine (CYT) have all demonstrated efficacy in mitigating nicotine withdrawal (6).

Varenicline functions as a partial agonist of the brain’s α4β2 subtype of the nicotinic acetylcholine receptor (nAChR), a receptor closely associated with nicotine dependence (7). Operating as a partial agonist, its mechanism involves both agonistic properties, capable of moderating symptoms associated with nicotine withdrawal, and antagonistic properties, which can reduce the pleasurable effects of nicotine (8, 9).

CYT is a quinolizidine alkaloid of natural origin extracted mainly from the seeds of plants that are part of the *Leguminosae* family, including *Cytisus Laburnum,* and, such as varenicline, is a partial agonist of the nAChR (10–13).

CYT has the ability to act as a partial agonist, and its strong affinity for the subtype receptor α4β2 counteracts the addictive properties of nicotine, reducing withdrawal symptoms (14, 15). After nAChR binding with CYT, the restrained release of dopamine could block the effect of nicotine from tobacco on the receptor (16, 17). In particular, several studies have indicated that in the context of nicotine addiction, the administration of CYT may have a dual impact. On one hand, it could modestly elevate dopamine levels within the mesolimbic system, reaching approximately half the levels induced by nicotine. On the other hand, CYT might mitigate withdrawal symptoms, reducing the sudden spike in dopamine levels linked to the rapid absorption of nicotine typically associated with cigarette smoking (18, 19).

The first clinical study on CYT was carried out in 1965, and in the following 10 years, different studies were conducted in many European countries such as Bulgaria, Poland, Germany, and Russia (20, 21). The findings achieved by these trials kicked off the widespread use of the CYT commercial product branded TABEX®, which was first marketed in Bulgaria in 1964 and then became widely available in former socialist economy (FSE) countries, including Poland (22). After the establishment of the European Union (EU), some FSE countries joined it, and TABEX® was withdrawn from some of them. However, TABEX® is still prescribed in Poland (7, 23). In Italy, CYT has been available since 2015 and is currently classified as an active pharmaceutical ingredient (API). Since no CYT-based pharmaceutical products are commercially available in Italy, CYT is imported in the form of raw material, which can be purchased by territorial and hospital pharmacies (HPs) for galenic capsule production. According to Italian law, CYT galenic capsules can be sold and dispensed to patients only under medical prescription.

Due to its natural and traditional origin, CYT’s development is characterized by an unusual history, and standard preclinical research to establish the optimal dosage, which would normally precede randomized clinical trials, was not carried out. To assess CYT pharmacokinetics, many studies were conducted in animal models; however, pharmacokinetic data in humans are limited (24). Nevertheless, findings gathered from these studies revealed that the half-life of CYT is approximately 4.8 h, with 95% being eliminated through urine unmodified (25, 26). A further important aspect of CYT’s pharmacokinetics is that there is no hepatic metabolism, and it is possible to exclude drug–drug interactions (27). The West dosing schedule (1.5 to 9 mg/day for 25 days) has been licensed for CYT in several countries, and it was used in an observational study in which participants treated with CYT had significantly high quit rates to suggest efficacy (7).

According to West et al. in 2011, CYT treatment is generally well tolerated. In fact, in this clinical trial, CYT is not associated with an increased risk of adverse events compared to placebo, although gastrointestinal symptoms are more frequent than placebo. The most frequent adverse reactions reported are abnormal dreams, insomnia, changes in taste, dry mouth and throat, decreased appetite, and, less frequently, nausea. Some patients have experienced headaches and irritability on the initial day of treatment. It is also noted that elevated doses of CYT can lead to dizziness and muscle weakness. However, reducing the dosage has been shown to alleviate these side effects. Importantly, CYT does not induce psychophysical alterations, making it suitable for individuals who drive vehicles or operate machinery (28, 29).

In Italy, the use of CYT is promoted by the Veneto regional program “Coordination and development of the Veneto system of tobacco treatment” for active smokers, especially those who smoke more than 15 cigarettes per day and are both available and motivated to quit smoking.

Since 2016, the galenic laboratory of HPs in the Integrated University Hospital of Verona (IUHVR), Veneto (Italy), has provided 1.5 mg CYT galenic capsules for in-hospital treatment for patients.

One of the advantages of introducing CYT in a hospital setting is to decrease costs related to NRT during hospitalization. In addition, the low cost of CYT could encourage its use after discharge, thus minimizing the risk of relapse and encouraging therapeutic continuity. It is important to emphasize that CYT is, by far, the cheapest anti-smoking option, compared to other pharmacological interventions, making it particularly appreciated, especially by heavy smokers, who generally require higher therapeutic doses and longer treatment periods (19). Therefore, CYT may be an attractive choice for smokers due to its lower cost in comparison to other pharmacotherapies.

Although actual knowledge about CYT’s pharmacokinetics suggests few drug interactions, the administration in hospitalized patients, who often present co-morbidity and polypharmacotherapy, has not yet been investigated. This protocol describes a prospective observational study to investigate the safety of CYT prescribed to a sample of smoking patients in a hospital setting.

The findings from this study will enhance our understanding of CYT management, promoting smoking cessation intervention through the use of an effective and safe substance as part of an integrated cessation and relapse prevention intervention.

## Methods

### Objectives of the study

The primary objective of the study is to assess the safety of CYT treatment in hospitalized smokers admitted to IUHVR.

The secondary objectives of this study are to assess patient’s compliance with CYT treatment and the efficacy of CYT treatment.

### Study design

This study is a monocentric, observational prospective investigation involving smoking patients admitted to IUHVR and treated with CYT for smoking cessation.

### Clinical endpoints

The primary endpoint of the study is to assess the safety of CYT adverse events (AEs) or adverse drug reactions (ADRs) reported by participants, which will be collected.

AEs are defined by the Italian Legislative Decree 211/2003 as “any harmful clinical event that occurs in a patient or in a person involved in a clinical trial that has been given a medicinal/device product and does not necessarily have a causal relationship with this treatment.” Indeed, ADRs are defined as follows: “all untoward and unintended responses to an investigational medicinal product related to any dose administered.” The definition also covers “medication errors and uses outside what is foreseen in the protocol, including misuse and abuse of the product” (Directive 2001/83/EC, Ministerial Decree 30 April 2015-GU No. 143).

For the European Regulation (Directive 2001/83/EC), serious adverse events (SAEs) or serious adverse reactions (SARs) are defined as “any unwanted medical event or device failure that results in the following outcomes: is fatal (causes death), is life-threatening (an event in which the patient was at risk of death at the time of the event), requests hospitalization or extension of hospitalization in progress, determines persistent or significant degree disability or incapacity, corresponds to a congenital anomaly/birth defect, is medically significant, or requires intervention to prevent one of the other outcomes listed above.”

If an AE occurs, the physician, supported by the clinical monitor (CM), will evaluate the event/treatment correlation to determine if an AE could be an ADR. At each visit or follow-up, AEs and ADRs reported by participants will be recorded by the CM in the CRF. In case of an ADR, the physician or the CM will fill out the online reporting form on the AIFA website (https://servizionline.aifa.gov.it/schedasegnalazioni/#/). The textual descriptions will be summarized in the report forms and will be coded according to standard terms in the Medical Dictionary for Regulatory Activities (MedDRA).

The secondary endpoints of the study are to assess the efficacy and compliance of CYT treatment. Self-reported 7-day and 15-day point prevalence abstinence (PPA) will be assessed at each study timepoint. A relapse will occur when patients smoke 7 or more cigarettes for 7 consecutive days or 2 consecutive weeks.

Biochemically verified abstinence will be evaluated using exhaled carbon monoxide (CO) measurement during in-person visits. A relapse is considered when CO value ≥9 ppm (non-smoker value <4.5 ppm) (30, 31).

To assess CYT treatment compliance, patients will be provided a study diary in which capsule intake or self-reported treatment adherence can be reported.

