**Figure 1 fig1:**
[figure not shown]
Study protocol timeline. QD, quit day.

After the baseline visit, two visits (visit 1 at day 7 and visit 2 at the end of treatment, day 25) and three follow-ups (visit 3 at 3 months, visit 4 at 6 months, and visit 5 at 12 months) will be conducted (see Table 1). Visits 1, 2, and 3 will be conducted face-to-face. The last two visits (visits 4 and 5) will be conducted via telephone.

**Table 1 tab1:** Protocol timeline procedure of visits and follow-up for patients enrolled in the CITOSP trial.

Procedure	Visit 0	QD*	Visit 1	Visit 2^§^	Visit 3	Visit 4	Visit 5
Informed consent	√						
Inclusion/exclusion criteria	√						
Demographic characteristics	√						
Clinical history	√						
Smoking history and status	√						
Cytisine treatment		√	√	√			
Adverse events			√	√	√	√	√
Adverse drug reactions			√	√	√	√	√
Self-reported abstinence (PPA)			√	√	√	√	√
Biochemically verified abstinence (exhaled CO)			√	√^#^	√^#^		

QD, quit day.

PPA, point prevalence abstinence.

CO, carbon monoxide.

^#^Only if the visit is in person.

*First day of treatment. ^§^Stop treatment.

Each control visit resulted in the collection of the following records:

Visit 0 (baseline visit): informed consent dated and signed, participant identification code, and socio-demographic characteristics of the participant (age, sex, education, and occupation). Smoking history: age at which cigarettes were first smoked and efforts to quit smoking (number of times, date of last attempt, and use of some drugs to quit smoking). Smoking Status: average amount of cigarettes smoked in the last month, average cigarettes for the year, the score obtained in the FTND test, and use of other forms of nicotine delivery (for example, e-cigarettes). Clinical history: pathologies and ongoing pharmacological treatments. Integrated therapeutic: This statement outlines the non-pharmacological approaches used in the study to help patients, including counseling, cognitive-behavioral education, lifestyle changes, and the possible use of smoking cessation tools.

QD (first day of abstinence): start of integrated therapeutic plan with CYT.

Visit 1 (7^th^ from QD): continuation of the integrated therapeutic plan with CYT, evaluation of AEs, evaluation of ADRs, evaluation of PPA, number of cigarettes smoked (in case of quit failure), and exhaled CO.

Visit 2 (25^th^ day from QD): end of treatment with CYT, evaluation of AEs, evaluation of ADRs, evaluation of PPA, and exhaled CO.

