### Cytisine dosing schedule

The West dosing schedule consisted of six 1.5 mg capsules per day (one capsule every 2 h) for 3 days (days 1 to 3), five capsules per day for 9 days (days 4 to 12), four capsules per day for 4 days (days 13 to 16), three capsules per day for 4 days (days 17 to 20), and two capsules per day for the final 5 days (days 21 to 25) (see Table 2). The target quit date was scheduled for the first day of treatment (day 1) (7).

**Table 2 tab2:** West dosing schedule (7).

Day of treatment	N° of capsules/die	Frequency of administration
Days 1–3	6	1 capsule every 2 h
Days 4–12	5	1 capsule every 2.5 h
Days 13–16	4	1 capsule every 3 h
Days 17–20	3	1 capsule every 4 h
Days 21–25	2	1 capsule every 6 h

In the case of patients with stage IV or V chronic kidney failure, the CYT dosing schedule consisted of three 1.5-mg capsules per day for 12 days (days 1 to 12), two capsules per day for 8 days (days 13 to 20), and finally one capsule per day for the last 5 days (days 21 to 25) (see Table 3).

**Table 3 tab3:** Cytisine dosing schedule adapted to patients in stage IV or V chronic kidney failure.

Day of treatment	N° of capsules/die	Frequency of administration
Days 1–12	3	1 capsule every 4 h
Days 13–20	2	1 capsule every 6 h
Days 21–25	1	1 capsule every 12 h

Concomitant medication use during CYT treatment will be allowed, evaluated, and documented at each visit, and any possible interactions with CYT will be verified.

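### The primary safety endpoint rests on participant reports taken during treatment only at days 7 and 25, with no symptom capture described in between, so mild, brief events may be missed or mis-dated

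*Protocol article*

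**What the plan says.** In the Protocol article, Clinical endpoints defines the primary endpoint through adverse events (AEs) or "adverse drug reactions (ADRs) reported by participants, which will be collected". The same section gives the recording rule: "At each visit or follow-up, AEs and ADRs reported by participants will be recorded by the CM in the CRF".

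The schedule under Figure 1 has "two visits (visit 1 at day 7 and visit 2 at the end of treatment, day 25") and then "three follow-ups (visit 3 at 3 months, visit 4 at 6 months, and visit 5 at 12 months"). Table 1 marks AEs and adverse drug reactions (ADRs) at Visits 1 to 5 and not at quit day, which is the first day of treatment. Visits 4 and 5 are by telephone.

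Under Cytisine dosing schedule, the standard course starts with "six 1.5 mg capsules per day (one capsule every 2 h) for 3 days (days 1 to 3"). It continues with "five capsules per day for 9 days (days 4 to 12), four capsules per day for 4 days (days 13 to 16"), then three a day on days 17 to 20 and two a day on days 21 to 25.

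On the diary, Clinical endpoints says "patients will be provided a study diary in which capsule intake or self-reported treatment adherence can be reported". Participant recruitment adds that it supports correct intake. Neither place mentions symptoms.

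On timing of reactions, the Introduction says "Some patients have experienced headaches and irritability on the initial day of treatment", and it links dizziness and muscle weakness to elevated doses.

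Sample size and statistical analysis plans the incidence of AEs and ADRs with 95% confidence intervals to day 25 and to 12 months. It plans no analysis by dose level.

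**The concern.** The study describes one treated group. The absolute incidence is the safety result, and incomplete ascertainment cannot cancel against a control arm. Missed events can only lower the rate, which makes the treatment look safer.

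The first AE question on the standard schedule comes after the days of highest intake, and the second asks about 18 days at once. A brief, mild symptom on day 1 or 2 is the kind of event that a patient may forget by day 7, or remember without a date.

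Dating matters here because quit day is also treatment day 1. Nicotine withdrawal and early drug reactions can fall in the same days. The physician's judgement on whether an AE is an ADR is easier when the symptom can be set against recorded intake. The diary would hold the intake side of that comparison but, as described, not the symptom side.

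**Working it through.** **The plan's own figure.** Inputs from Sample size and statistical analysis: incidence 20%, two-sided 95% interval, total width 10 points, n = 264. The Clopper-Pearson interval at the expected count (0.20 × 264 = 52.8) runs from 15.3% to 25.3%, a width of 9.99 points. At n = 263 the width is 10.01 points. The stated 264 is therefore reproduced, and this point alleges no sample-size error.

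**Intake covered by each on-treatment contact, standard schedule.**
- Total: 6×3 + 5×9 + 4×4 + 3×4 + 2×5 = 18 + 45 + 16 + 12 + 10 = 101 capsules, as the article states.
- Days 1 to 3: 18 capsules, 18/101 = 18%. Seen from day 7 they lie 7 − 3 = 4 to 7 − 1 = 6 days back.
- Day-7 contact, days 1 to 7: 18 + 5×4 = 38 capsules, 38/101 = 38%, at two dose levels.
- Day-25 contact, days 8 to 25: 18 days, 101 − 38 = 63 capsules, at four levels (5, 4, 3 and 2 a day) with three changes between them.

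**Stage IV or V kidney failure.** Intake is three a day on days 1 to 12, so the highest level is still running at day 7. The argument about days 1 to 3 as a separate peak does not apply to these patients. The look-backs of 7 and 18 days do.

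**After treatment.** The intervals are day 25 to 3 months, 3 to 6 months and 6 to 12 months. These longer look-backs bear on the 12-month rate.

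**Possible size.** The documents give no rate of under-reporting, so the capture fractions below are an assumption. Observed incidence = 20% × fraction of affected patients captured, with the Clopper-Pearson 95% interval at n = 264:

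| Captured | Observed | 95% interval |
|---|---|---|
| 100% | 20% | 15.3% to 25.3% |
| 90% | 18% | 13.6% to 23.2% |
| 80% | 16% | 11.8% to 21.0% |
| 70% | 14% | 10.1% to 18.8% |

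The shift is 2 to 6 points, against a planned half-width of 5. At 80% capture the interval still includes 20%; at 70% it does not.

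**The case against.** **Onset dates and dose.** A reader might infer that events cannot be tied to dose at all. The article does not support that. It neither says nor rules out that onset dates are recorded, and such a field is commonly left to the full protocol or the CRF. With an onset date, the fixed day-by-day schedule places any event at a dose level. The article also promises no analysis by dose.

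**Recall is not the only route.** Patients start as inpatients, are told about common ADRs and receive emergency contact details. The physician's assessment of an AE is not tied to a visit. Reporting between visits is therefore possible. This stands, but an emergency contact is unlikely to bring in a dry mouth or a bad dream, and patients may be discharged during the course.

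**The nature of the reactions.** It is tempting to say that most of the listed reactions are short-lived and dose-related. The Introduction gives no durations. It places only headache and irritability on the first day and links only dizziness and muscle weakness to elevated doses, without saying that six capsules a day counts as elevated.

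**Size.** The analysis is an incidence, so if patients are counted, one remembered event is enough to count a patient. The 20% is itself a reported rate from a cited study, whose way of collecting events cannot be seen here. The safety analysis is descriptive and has no threshold that a shift would cross. All of this stands. It limits the conclusion to possible loss, of unknown size.

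**Conclusion.** The point holds as a weakness in how the primary endpoint is collected. The contact schedule, the recording rule and the diary's purpose are all stated, so the point does not rest on silence alone. Mild and transient events may be missed or mis-dated, especially those from days 1 to 3 of the standard schedule, and any loss lowers the incidence.

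The amount cannot be calculated from the documents. The 14% to 18% is an illustration that assumes a true incidence of 20% and capture of 70% to 90% of affected patients. It also assumes that the patients lost have no other event that they report. The documents do not support saying that under-counting is established, or that events cannot be related to dose. This is a cheap improvement worth making; it does not invalidate the design.

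**What to change.** Add one dated line per day to the existing diary for days 1 to 25: new symptom today, yes or no, and what. The clinical monitor reconciles these entries with the patient at Visits 1 and 2. Record onset and stop dates in the eCRF, if this is not already done, and say so in the protocol.

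Incidence by dose step need not be required. The steps last 3, 9, 4, 4 and 5 days, and on a fixed descending schedule dose cannot be separated from time since quit day. If it is shown, it should be descriptive and per person-day.

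The cost is one diary line and at most two date fields, with no extra visit. Patients carry slightly more burden. More mild events will be recorded, so the rate may be less comparable with the cited 20%; the report should state how events were collected.

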### Sample size and statistical analysis

Assuming an overall incidence of all AEs and ADRs equal to 20% as reported by Hajek et al. (28), 264 subjects will be needed to produce a bilateral confidence interval of 95% with an amplitude of 10%. This number will be increased to 300 subjects to compensate for a potential loss of 14% of subjects during the 12-month follow-up. To recruit 300 subjects, it will take 36 months. The total duration of the study will be 4 years.

All variables recorded in the study will be presented using the plus descriptive statistic appropriate to their nature. Continuous variables will be presented with mean and standard deviation with median and interquartile distance based on their distribution; ordinal and categorical variables will be presented with frequency and percentage.

To assess the safety of treatment with CYT, the incidence of AEs and ADRs will be evaluated, with respective 95% confidence intervals (CIs) up to the end of treatment (day 25) and up to 12 months from the start of the treatment (quit day). The percentage of subjects will be calculated to assess the compliance of patients with CYT treatment who respected their dosage schedule with the respective 95% CI.

To evaluate the efficacy of CYT treatment, the percentage of subjects who reported abstinence in the previous 7 days and 15 days (7-day PPA and 15-day PPA) before each study timepoint will be calculated. For in-person visits and follow-ups, the PPA will be biochemically verified through exhaled CO measurement.

The efficacy will also be studied at a multivariate level to assess whether the positive/negative outcome of the treatment is associated with certain demographic and/or clinical factors. For this type of analysis, they will construct logistic regression models by setting the (yes/no) relapse evaluated as dependent variables according to the reported and objective efficacy criteria at the end of treatment (25^th^ day from the start of treatment) and 12 months from the start of treatment. The independent variables will be chosen based on the assumptions of experimenters on possible predictors of efficacy, including the result of the FTND, the ward, the primary cause of admission, sex, age, education, occupation, age in which the person started smoking, and number of previous smoking cessation attempts.

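### The primary safety endpoint and its recording rule are worded as participant-reported, which does not match the protocol's own AE and SAE definitions; state that events are collected from all sources

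*Protocol article*

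**What the plan says.** All references are to the protocol article.

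- **Clinical endpoints, primary endpoint.** The safety endpoint consists of AEs or "adverse drug reactions (ADRs) reported by participants, which will be collected".
- **Clinical endpoints, recording rule.** At each visit or follow-up, "AEs and ADRs reported by participants will be recorded by the CM in the CRF".
- **Abstract.** At each visit, "any adverse events or adverse reactions reported by patients following the intake of CYT will be evaluated".
- **Clinical endpoints, definitions.** An AE is "any harmful clinical event that occurs in a patient or in a person involved in a clinical trial" who has been given the product, whether or not the product caused it. An SAE is an event that, among other outcomes, "is fatal (causes death), is life-threatening". Incapacity and a prolonged hospital stay also qualify.
- **Clinical endpoints, physician's role.** "If an AE occurs, the physician, supported by the clinical monitor (CM), will evaluate the event/treatment correlation".
- **Visits and follow-ups.** Contacts are at day 7, day 25 and 3, 6 and 12 months. "The last two visits (visits 4 and 5) will be conducted via telephone".
- **Sample size and statistical analysis.** AE and ADR incidence is reported with 95% confidence intervals to day 25 and to 12 months. The target of 264 is raised to 300 "to compensate for a potential loss of 14% of subjects during the 12-month follow-up".

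**The concern.** The definitions and the recording rule describe two different sets of events. The definitions cover anything harmful that happens to a participant. The rule covers what the participant tells the clinical monitor. The sets differ where safety matters most. A participant cannot report their own death and may be unable to report an incapacitating event. A participant may also not know of, or not mention, something that ward staff saw or that stands only in the record.

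The Introduction and Discussion justify the study by the lack of safety data in hospitalized patients with co-morbidities and several concomitant drugs. In that population, events noticed by staff rather than by the patient are to be expected. If they have no route into the CRF, the primary estimate is too low, and the serious events are the most depleted.

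**Working it through.** **1. The plan's own figure.** Inputs from the sample-size section: incidence 20%, two-sided 95% interval, total width 10 points. The smallest n for which the exact (Clopper-Pearson) interval at x = 0.20n is no wider than 0.10 is n = 264, with width 0.0999 (15.35% to 25.34%). The stated 264 is reproduced. The rise to 300 is close to 264/(1 − 0.14) = 307. These figures neither support nor weaken the point; they show that the endpoint is planned as a proportion of subjects, with a half-width of about 5 points.

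**2. Definitions against the recording rule.**

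| Type of event | Within the AE/SAE definitions? | Reaches the CRF under the rule as worded? |
|---|---|---|
| Symptom the participant mentions | Yes | Yes |
| Death | Yes | No, the participant cannot report it |
| Incapacitating event | Yes | Not while the participant is unable to report |
| Event known only to staff or the record | Yes | No stated route |

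The sentence on the physician does not fill the gap. It describes causality assessment once an AE exists and gives no step for finding AEs.

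**3. Direction of the error.** Let E of N participants truly have an event, and let k of them have no event recorded.

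- If the k stay in the denominator as event-free, the observed incidence is (E − k)/N, which is below E/N.
- If the k drop out of the analysis, it is (E − k)/(N − k). This is also below E/N whenever E < N.

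Both routes lower the estimate. A participant counts towards k only if no other event of theirs was recorded, so one missed event in someone with an earlier recorded AE leaves the overall proportion unchanged. It would still distort the count of serious events.

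**4. Size.** The documents give no share of unreported events, so no corrected figure can be derived. The following is illustration on assumed values only: N = 264, true incidence 20% (E = 52.8), and a share m of affected participants missed, so k = 52.8m. The exact interval is at the expected count with the k kept in the denominator.

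| m (assumed) | Kept: 0.20(1 − m) | Bias (points) | Exact 95% CI | Dropped: (E − k)/(N − k) |
|---|---|---|---|---|
| 2% | 19.6% | −0.4 | 14.99% to 24.91% | 51.744/262.944 = 19.7% |
| 5% | 19.0% | −1.0 | 14.45% to 24.26% | 50.16/261.36 = 19.2% |
| 10% | 18.0% | −2.0 | 13.56% to 23.18% | 47.52/258.72 = 18.4% |
| 20% | 16.0% | −4.0 | 11.79% to 20.99% | 42.24/253.44 = 16.7% |

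Each interval still contains 20%. With a true incidence of 30% and 20% missed (both assumed), the observed incidence is 0.30 × 0.80 = 24.0%, a bias of −6.0 points, and the interval of 18.98% to 29.62% excludes 30%.

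**5. Which estimate is exposed.** Treatment lasts 25 days, with face-to-face visits at days 7 and 25. Recall gaps there are short, though events known only to staff could still be missed. After month 3 the gaps are three months (months 3 to 6) and six months (months 6 to 12), each ending in a telephone call. The 12-month estimate therefore carries most of the risk.

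**The case against.** The strongest defence is that the text is loose rather than restrictive. It never says that participant report is the sole source, and it never excludes deaths or staff-observed events. It expressly places fatal and life-threatening events in scope. The physician's assessment is triggered by an AE occurring, not by a patient reporting one. Table 1 labels abstinence as self-reported but puts no such label on AEs or ADRs. The ethics section commits the study to Good Clinical Practice and mentions pharmacovigilance. A journal article also condenses the full protocol, which may set out SAE notification and record review.

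Much of this stands, and it rules out three stronger readings.

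- A reader might infer that participant report is the only permitted source, so that serious events will certainly be missed. The documents name one source but do not exclude others; the loss is conditional on the rule being followed as written.
- A reader might infer that participants who die or become incapacitated are treated as part of the 14% loss. The sample-size section does not say how deaths are classified.
- A reader might attach a definite number of percentage points to the bias. No input for that is in the documents, and the answer also depends on whether such participants stay in the denominator.

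The defence does not remove the mismatch. The article does not merely leave the source unstated: it states one three times, in the endpoint, the recording rule and the Abstract, and that source cannot deliver the events its definitions include. If the full protocol provides wider capture, this text misdescribes the primary endpoint and should be brought into line with it.

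**Conclusion.** The concern holds as a mismatch between the participant-reported wording of the primary endpoint and the AE and SAE definitions in the same section. If the rule is applied as written, the incidence can only be understated, chiefly to 12 months and chiefly for serious events. The amount is unknown; the 0.4 to 6.0 point range in the illustration rests wholly on assumed true incidences of 20% and 30% and assumed missed shares of 2% to 20%. The conclusion assumes that no other document already provides all-source capture. The point is best classed as a cheap improvement. It does not show that the study will fail to record deaths or that its safety conclusion is invalid.

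**What to change.** Amend the recording rule in Clinical endpoints, and align the endpoint sentence and the Abstract with it:

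1. Record AEs, ADRs and SAEs from participant report, from treating staff, and from review of the hospital record by the clinical monitor at discharge and at each study timepoint.
2. For participants who cannot be reached, check vital status and readmission in the hospital record.
3. Count a death or serious event found in this way as an AE, not as loss to follow-up.

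The study runs at one hospital and the clinical monitor is already in place, so the cost is a wording amendment and some extra monitor time. The reported incidence would probably be somewhat higher than under participant report alone. One limit remains: the hospital's record may not show events treated elsewhere.
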